## Abstract

**Background:**

Depression is among the leading causes of disability worldwide. Not all people with depression respond adequately to standard treatments. An innovative therapy that has shown promising results in controlled trials is music therapy. Based on a previous trial that suggested beneficial effects of integrative improvisational music therapy (IIMT) on short and medium-term depression symptoms as well as anxiety and functioning, this trial aims to determine potential mechanisms of and improvements in its effects by examining specific variations of IIMT.

**Methods/design:**

A 2 × 2 factorial randomised controlled trial will be carried out at a single centre in Finland involving 68 adults with a diagnosis of depression (F32 or F33 in International Statistical Classification of Diseases and Related Health Problems 10th revision). All participants will receive 6 weeks of bi-weekly IIMT, where they are invited to improvise music and reflect on those improvisations with a music therapist in a one-to-one setting. Potential enhancements to IIMT will include: home-based listening to recorded improvisations (LH) from IIMT sessions to facilitate integration of therapeutic processing into daily life; and resonance frequency breathing (RFB), a breathing exercise at the beginning of each session to facilitate emotional expression and processing. Participants will be randomised in a 1:1:1:1 ratio into each combination (IIMT alone or with one or both enhancements). The primary outcome is depressive symptoms measured by the Montgomery–Åsberg Depression Rating Scale (MADRS) at 6 weeks. Secondary outcomes are depressive symptoms at 6 months; anxiety, quality of life, and functioning at 6 weeks and 6 months; and adverse events. Secondary underlying mechanisms/process variables are self-rated momentary depression level before every IIMT session; and homework compliance in IIMT + LH. Statistical analyses involve an intention-to-treat approach, using a linear mixed-effects model examining the main effects (LH vs no LH; RFB vs no RFB) and interaction effects (LH × RFB).

**Discussion:**

This trial will contribute to understanding the mechanisms of IIMT and may further enhance the effectiveness of an intervention that was previously shown to be superior to standard care alone for adults with depression.

**Trial registration:**

ISRCTN11618310. Registered on 26 January 2018.

## Background

Depression is one of the psychiatric disorders that can effectively be treated through music therapy [1]. In previous music therapy trials for depression, diverse clinical techniques relying on multiple methods have been employed. However, Erkkilä et al. [2] showed that applying only one clinical technique—in that case clinical improvisation—was effective as well. Thus, the previous evidence does not exclusively speak for multimethod clinical approaches. Along with the increased evidence favouring music therapy as an effective form of treatment for depression, there is a need to take the next step—to identify the active ingredients of music therapy, meaning the elements that enhance patient outcomes [3]. This is important in particular because although Erkkilä et al. [2] found that many participants responded to usual improvisational music therapy, proving it to be effective on the group level, there were also those clients who did not respond or who responded less than others. This finding raises the question of whether the efficacy of clinical improvisation can be further enhanced in order to increase the response rate.

### Integrative improvisational music therapy

One of the specific music therapy techniques that has been demonstrated to be effective in the treatment of depression is integrative improvisational music therapy (IIMT). IIMT is a model that is built on a versatile theoretical background. It was originally rooted in psychoanalytical ideas about the meaning of music [4, 5], in improvisational music therapy used in a psychodynamic context [6], as well as in psychodynamic psychotherapy [7]. This legacy is still important for IIMT. However, along with the development of integrative psychotherapy [8], which emphasises the needs of the client in changing situations instead of closely following certain, tightly framed theoretical or practical guidelines and rules, it became natural to definitionally update our model and better describe the flexible clinical thinking and practice associated with it. Therefore, in addition to being psychodynamic at its core, IIMT also involves supportive psychotherapy, which integrates psychodynamic, cognitive-behavioural, and interpersonal views [9] as well as resource-oriented music therapy [10], which, among other things, redefines the nature of the therapeutic relationship.

The unique and essential component [11] of IIMT is the clinical improvisation. The sessions consist of a combination of improvising in a client–therapist dyad and discussing the experiences triggered by the improvisations [12]. As a form of non-verbal expression and interaction, clinical improvisations lead to the emergence of abstract and unshaped mental contents that are often accompanied by emotional content. A clinical improvisation typically triggers emotions, emotional memories, images, metaphors, and associations, which can be further processed in the verbal domain [13]. In essence, musical improvisation serves as the experiential foundation for meaning formation.

Improvisational music therapy is suitable for basically all client groups without the need for specific musical training, and can be successfully applied even when one’s ability for verbal expression is limited [13, 14]. Any adult with normally developed cognitive skills and abstract thinking is able to connect symbolic and experience-based mental contents to their musical expression in clinical improvisations. They are also able to verbalise, in other words to further process, their music-based experiences and to interpret these experiences in the light of their current life situation [15].

### Processing of difficult emotions as an active ingredient

Our experience in working with adults with depression has shown that clinical improvisations often trigger anxious, negative emotions and experiences related to the illness. Furthermore, the clients appear to improve through IIMT particularly if dealing with these challenging emotions. We therefore started hypothesising that there is something in improvisational music therapy which especially facilitates the emergence of traumatic material and negative emotions, yet in a way that is tolerable to the client. When looking at the literature, a recurrent finding is that emotional processing plays a key role in achieving a positive therapeutic outcome. Increased emotional processing generally leads to better outcomes, while avoidance and suppression worsen the conditions [16, 17]. Expressing, accepting, and transforming the unwanted thoughts and related negative emotions is essential for psychotherapy to be successful; as Hunt [18] pertinently summarised, “the only way out is through”.

Several definitions of emotional processing have been proposed [19]. However, based on the ideas developed by Greenberg and Pascual-Leone [20], at least the following appear to be core ingredients: certain emotions are activated (arousal); the client is able to acknowledge, allow, and tolerate these emotions by finding a middle ground between avoidance and over-engagement (regulation); and the emotional experience is explored and reflected upon, for example, through symbolisation and meaning-making. This definition would apply to emotional processing in any form of emotion-focused or experiential therapy, including music therapy, whose mode of action is essentially emotion based [21].

### Music listening as promoter of emotional processing

The special potential of music to facilitate the processing of complex negative emotions is supported by music psychology research. Music listening has been shown to induce complex emotional experiences [22, 23], and to support elaborate self-regulatory processing of sometimes difficult, personal emotional states in everyday life [24]. Furthermore, music is often characterised—somewhat paradoxically—by pleasurable experiences of difficult emotions, such as sadness [25]. It has been argued that the enjoyment of sadness in music is explained by the capacity of music to allow simultaneous absorption, yet dissociation, from the affective content [26, 27]. Music characteristically allows access to various degrees of emotional nuances and intensities with simultaneous self-reflection, detachment, and elaborative awareness of these emotional nuances [28], supporting both experience and conceptual awareness of feelings [29]. Overall, the findings support the idea that music holds special potential for the self-reflective processing of complex, difficult, and even painful emotions.

However, music listening patterns have been shown to differ in terms of how adaptive and health beneficial they are, and depressed individuals in particular are inclined towards using the unhealthy/maladaptive patterns [27, 30–33]. Depressed individuals thus are generally less able to benefit from the affordances of music, but pioneering work indicates that music therapy interventions can help the clients to learn more health-beneficial ways of using music in their own daily lives [34]. When the music listening experience is combined with the therapy process and targeted towards the clinical improvisations created during therapy, it becomes possible to focus more on adaptive patterns (e.g. reflection instead of rumination). The listening-back experiences can then further be discussed and processed with the therapist during the sessions. This is expected to result in an upward spiral of adopting resources for reflecting on personal experiences in an adaptive manner, with the possibility of transferring such accomplishments in therapy to the client’s everyday life. This could potentially be highly relevant, particularly in terms of sustaining the long-term impact of the therapy.

In sum, we propose that combining music making (improvising) and music listening (listening back to the recorded clinical improvisation as homework) has mutually complementary effects on therapeutic processing. Listening back to the improvisations may particularly promote the self-reflective processing of the emotions and personal experiences expressed through the improvisation. We therefore aim to assess the combined effect of improvisation and listening activities.

### Resonance frequency breathing as a promoter of emotional processing

Starting the therapy sessions with a specific type of slow breathing is another avenue we wish to explore. The purpose of this preliminary intervention would be to relax the clients and prepare them for deeper therapeutic work. Indeed, one well-known benefit of slow breathing is to reduce autonomic arousal, which can be observed in pranayama yoga for example [35, 36]. It should be noted that the idea to start psychotherapy sessions with a breathing intervention has already been proposed by other authors [37, 38]. However, this suggestion has been very little implemented. Usually, when a breathing intervention is systematically used for emotional or psychological disorders, it is in the form of a stand-alone intervention, with no integration into another, primary psychotherapeutic method.

The breathing intervention we will be using is known, among other names, as resonance frequency breathing (RFB), which is the core component of a method called heart rate variability biofeedback (HRVB). The idea behind HRVB is to help clients breathe at their resonance frequency, through which they achieve a state known as psychophysiological coherence [39]. This state of resonance or coherence has two main characteristics, clearly detectable on the physiological level: the amplitude of heart rate oscillations is maximised, while the heart, respiratory, and blood pressure rhythms become highly synchronised [40]. This results in an immediate shift of the autonomic nervous system towards parasympathetic (rest-and-digest) dominance, leading to a state of calm alertness. It should be noted that the optimal breathing speed under which resonance is achieved is different from person to person. However, we know from previous studies that for an adult the optimal speed is located somewhere around 6 breaths/min [41].

Regarding the potential benefits of using RFB in conjunction with IIMT, we have already collected some promising evidence through two single-case experimental studies involving a healthy client [42] and a client diagnosed with anxiety disorder [43]. The results indicate that RFB might be an adaptive intervention, capable of both supporting and challenging the client, depending on the therapy phase and the client’s current emotional needs. In the light of these exploratory results, we hypothesise that RFB will favour the emergence of difficult, negative emotions during therapy, while at the same time improving the client’s tolerance for and ability to process such emotions. Should this indeed be the case, we expect that the addition of RFB to IIMT will lead to better therapeutic outcomes, with better emotional processing being the mediator.

### Aims of the study

Self-reflective processing of negative emotions may well be a core ingredient in explaining the effectiveness of clinical improvisations and IIMT in general. Therefore, this study is designed to apply methods for enhancing this type of processing and testing their impact on the outcomes of IIMT in the treatment of depression. Two different types of methods will be added to create the experimental conditions of the trial—listening back to improvisations (LH) and resonance frequency breathing (RFB). The study’s main hypothesis is that the addition of LH or RFB will have a favourable effect on the therapy outcome. In addition, we will examine the internal mechanisms of IIMT in order to gain a better understanding of how they contribute to recovery. Lastly, we will examine whether IIMT has certain unique or exceptional characteristics that support its use in the treatment of depression in general.

## Method

### Study design

#### Participants, recruitment, and the site

Participants will be recruited in central Finland through announcements placed in local newspapers. Our experience has shown that this approach is more effective than targeting only mental health clinics and psychiatric polyclinics. We will repeat the announcements as often as needed for reaching the recruitment target. The trial will be conducted at the Music Therapy Clinic for Training and Research, Department of Music, Art and Culture Studies, University of Jyväskylä, Finland.

#### Inclusion and exclusion criteria

As inclusion criteria, the participants must be between 18 and 55 years of age and have depression as their primary diagnosis (categories F32 and F33 of the ICD-10), assessed by the Montgomery–Åsberg Depression Rating Scale (MADRS). In addition, if it is diagnosed alongside the depression, participants with anxiety will also be included, as both pathologies present a high level of comorbidity. Musical skills or any form of musical background are not required; their presence, however, does not constitute a reason for exclusion.

The exclusion criteria are psychosis, combined psychiatric disorders in which depression cannot be defined as the primary disorder, acute and severe substance misuse, and depression severity preventing the clients from participating in the measurements or engaging in verbal conversation. Furthermore, participants must be able to complete written questionnaires. Therefore, people with insufficient knowledge of the Finnish language or who are otherwise unable to complete such a questionnaire will be excluded.

#### Trial design and hypotheses

The study is a randomised 2 × 2 factorial trial, in which the conditions are derived from either the presence or non-presence of listening homework (LH) and resonance frequency breathing (RFB). The design is presented in Table 1. All groups receive IIMT. In addition, one treatment group receives LH as an additional component, the second treatment group receives RFB as an additional component, and the third treatment group receives both of these as an additional component.

**Table 1 Tab1:** Trial design: 2 × 2 factorial

Presence of additions	LH present (*n* = 34)	LH not present (*n* = 34)
RFB present (*n* = 34)	IIMT + LH + RFB (*n* = 17)	IIMT + RFB (*n* = 17)
RFB not present (*n* = 34)	IIMT + LH (*n* = 17)	IIMT (*n* = 17)

*IIMT* integrative improvisational music therapy, *LH* listening homework, *RFB* resonance frequency breathing

A decrease in depression scores is expected in all groups, as IIMT as such is already known to be effective in the treatment of depression [2]. In this study, we further hypothesise a significant main effect of both additional interventions:There will be a significant main effect of LH.There will be a significant main effect of RFB.

Based on this, we expect that each treatment group will show an increased improvement in comparison to the IIMT-only group. The greatest improvement in depression is likely to be observed in the group receiving both additional treatment components (IIMT + LH + RFB), but the investigation of the potential interaction effect of the additional treatments is kept exploratory. We also hypothesise faster recovery—an earlier drop in depression scores—in the enhanced treatment conditions compared to the IIMT-only condition.

#### Randomisation and sample size

Figure 1 shows how participants eligible for the randomised controlled trial (RCT) flow through the study from recruitment to follow-up. After screening and diagnosis, 68 participants will continue to take part in the study. Following a baseline assessment they will be randomly assigned to one of the four combinations of conditions (*n* = 34 in each condition; *n* = 17 in each combination).

**Fig. 1 Fig1:**
[figure not shown]
RCT flow chart with outcome measures. GAF Global Assessment of Functioning, HADS-A Hospital Anxiety and Depression Scale—anxiety subscale, IIMT integrative improvisational music therapy, LH listening homework, MADRS Montgomery-Åsberg Depression Scale, RAND-36 quality-of-life survey, RFB resonance frequency breathing

An external expert who has no direct contact with the patients will conduct a computerised randomisation procedure. We will employ block randomisation with randomly varying block sizes of 4 and 8. The allocation list will be saved on a password-protected repository with access only by the PI and study coordinator. To ensure allocation concealment, the randomisation will be conducted at another site (Uni Research, Bergen, Norway). As a result, the assessor, the therapists, and the participants will not be able to know the group allocation in advance. Only the outcome assessor will remain blinded to the group allocation throughout the trial. At the time of assessments, participants will be reminded not to reveal their allocation to the assessor. As far as the PI is concerned, he is blinded from the randomisation and the clients’ conditions in general, but because he is also one of the clinicians and participates in supervision he will get to know the condition of some clients. However, the PI is not involved in the client assessments or data entry in any way.

A power calculation was carried out for the primary outcome (depressive symptoms measured by the MADRS), based on the following assumptions.

Prior reviews of music therapy used in the treatment of depression have reported large effect sizes of music therapy compared to standard care. A recent meta-analysis [1], which included nine studies and involves a total of 421 participants, examined the short-term effect of music therapy for depression for primary outcomes. These authors found moderate quality evidence favouring music therapy and treatment as usual (TAU) over TAU alone for both clinician-rated depressive symptoms (SMD – 0.98, 95% CI – 1.69 to − 0.27, three RCTs, one CCT, *n* = 219) and patient-reported depressive symptoms (SMD – 0.85, 95% CI – 1.37 to − 0.34, three RCTs, one CCT, *n* = 142). Regarding IIMT specifically, our previous study found a medium effect size of *d* = 0.65 [2] based on the traditional two-arm design (intervention vs control).

As regards our additional components, a meta-analysis of the effect of HRVB training on stress and anxiety [44] reported large effect sizes with both the pre–post within-group effect size and the between-group analysis comparing HRVB to a control condition yielding Hedges’ *g* of around 0.8. A meta-analysis of the effects of homework assignments on treatment outcome in cognitive and behavioural therapies [45] reported a pooled ES of *d* = 0.48 favouring homework.

With the target sample size already reported (34 in each main effect), a two-sided *t* test at the 5% significance level will have 50% power to detect an effect size of 0.48 (LH) and a 90% power to detect an effect size of 0.8 (RFB). We provide these numbers with reservations and for information only, since these meta-analyses about homework and HRVB were not conducted in an identical setting to our trial. First of all, HRVB was studied as a stand-alone intervention, whereas we are using it in combination with another method. Second, the type of homework used in IIMT (listening back to self-created music improvisations) is arguably quite different from the homework usually given in cognitive behavioural therapies (e.g. exposure, thought diaries, or practice of social skills). Therefore, we acknowledge that the main effects of RFB and LH may be different from those found in the literature. Consequently, our study remains exploratory, and will only provide evidence for possible strong effects of the added components.

The minimum clinically important difference (MCID) for the Montgomery–Åsberg Depression Rating Scale (MADRS) has been reported to vary between 1.6 and 1.9-point changes from baseline when using a distribution-based method [46]. For anchor-based methods, prior studies report a remission cut-off point as a total score of < 9 points after treatment, or that a score of ≤ 5 equals complete or symptom-free remission and ≤ 11 equals remission, and that a decrease in 39% from baseline corresponds to “much improved” on the Clinical Global Impressions Scale. A mean difference of 1.6–1.9 points, with a common SD of around 7 [2], corresponds to an effect size of around 0.25, which is much lower than the effect size for which this study is powered. Thus, the study will not be able to reliably detect an MCID, but will be powered to detect an effect size similar to those found in previous related studies, as described earlier.

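### The PI, a treating clinician, can open the allocation list, which contradicts the stated PI blinding and leaves the stated allocation concealment unsupported

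*Protocol article*

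**What the plan says.** All the statements stand in the protocol article, Method, Randomisation and sample size, in the text after the Fig. 1 legend.

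- Generation: "An external expert who has no direct contact with the patients will conduct a computerised randomisation procedure". This happens at a separate institution, and the article gives that as the means of concealment.
- Storage: "The allocation list will be saved on a password-protected repository with access only by the PI and study coordinator".
- Concealment claim: "As a result, the assessor, the therapists, and the participants will not be able to know the group allocation in advance".
- Blinding during the trial: "Only the outcome assessor will remain blinded to the group allocation throughout the trial".
- PI blinding claim: "As far as the PI is concerned, he is blinded from the randomisation and the clients’ conditions in general". The sentence then makes one exception: "because he is also one of the clinicians and participates in supervision he will get to know the condition of some clients".
- Mitigation: the PI takes no part in assessing clients or entering data.

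The same section places randomisation after the baseline assessment and uses blocks of 4 and 8 in random order.

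**The concern.** Off-site generation conceals allocations only while the list stays away from those who treat clients or can influence their entry. Here it is stored where a treating clinician can open it. The section therefore credits the off-site step with a protection that its own access rule may remove, and it calls blind a person to whom it gives the list.

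Concealment and assessor blinding guard against different things. A blinded assessor protects the measurement of the MADRS. Concealment protects the comparability of the groups: who enters when, and which client goes to which therapist. Knowledge of allocation can also affect how a clinician treats and supervises. Both main effects (LH and RFB) rest on the same allocation list, so the point touches both. If the trial report repeats the two claims unchanged, it will make risk-of-bias statements that its own protocol does not bear out.

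**Working it through.** No figure in the plan depends on this point, so the main check is one of consistency.

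**Step 1. The premises.** (a) The PI can open the list. (b) The PI is a clinician in the trial. From (a) and (b), at least one therapist can open the list.

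**Step 2. Test each claim under both meanings of the list.** The article does not say which meaning applies.

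| Claim | List holds the full sequence, including future assignments | List holds only assignments already released |
|---|---|---|
| Therapists cannot know allocations in advance | Contradicted: one therapist can look them up | Not contradicted by the list itself |
| PI generally blind to the randomisation and to clients' conditions | Contradicted | Contradicted: the PI can look up any client already randomised |

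The PI-blinding claim fails in both columns. The only exception the article admits is what the PI learns about some clients through therapy and supervision; access to the list is not mentioned as a route. The concealment claim depends on a fact the article does not give.

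**Step 3. Do the varying blocks help?** Inputs: four arms in equal ratio, 68 participants, blocks of 4 and 8 (all from the article), with the two sizes taken as equally likely (an assumption). Suppose someone knows all past assignments and guesses the least-used arm.

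- Blocks of 4 only, averaging over the four positions: (1/4 + 1/3 + 1/2 + 1)/4 = 2.083/4 = 0.52.
- Mixed blocks of 4 and 8, by simulation: right about 48% of the time.
- Pure chance: 1/4 = 25%.
- Reading a list with future assignments: 100%.

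Varying block sizes hinder guessing but give no protection against someone who can read ahead. Even a list of past assignments leaves the next one more predictable than chance to the person who holds it.

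**Step 4. Which routes of influence remain?**

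- Eligibility: little scope. Recruitment is by newspaper announcement (Participants, recruitment, and the site). The MADRS is used to determine eligibility (Primary outcome), and a psychiatric specialist does all assessments (Assessment). No section gives the PI a part in this.
- Timing of entry: open, if future assignments were readable.
- Matching of clients to therapists: open but limited, since each of the 11 clinicians works in all four conditions (Treatment fidelity and training the clinicians).
- The PI's conduct as therapist, as supervision participant and as the contact when a client worsens (Safety assessments): open under either meaning of the list.

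**The case against.** The strongest reply is that the stored list may be a record of assignments already made. An external expert at another institution conducts the randomisation, and assignment follows baseline. That fits release of one participant at a time with local filing afterwards, and an article may leave the release procedure to the full protocol. This stands as a possibility, and it is why the concealment claim is called unsupported rather than false. It does not rescue the PI-blinding claim.

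A second reply is that the article is partly candid. It qualifies the PI's blinding, says only the assessor stays blind throughout, and keeps the PI out of assessment and data entry. All of this stands, and it protects the MADRS rating. It does not disclose the list as a route to unblinding.

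Three stronger readings are tempting, and the document supports none of them.

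- *The PI could see every upcoming allocation, so concealment was broken.* The content of the list is not stated, and access is not use.
- *The PI could steer who was enrolled.* Eligibility rests on an assessment in which the PI has no part.
- *The bias can be sized.* With SD 7 (Randomisation and sample size) and 34 v 34, a selection imbalance of 1 or 2 MADRS points gives a noncentrality of (1/7)√17 = 0.59 or (2/7)√17 = 1.18. The false-positive rate of a two-sided t test on 66 degrees of freedom then rises from 5% to about 9% or 21%. But those imbalances are pure assumptions, and the same percentages would follow from any cause. The planned repeated-measures mixed model, with MADRS also measured at baseline, could absorb part of a difference in baseline severity.

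**Conclusion.** The access rule and the PI-blinding statement contradict each other within one section, whatever the list held. The statement that therapists could not know allocations in advance is undercut unless the list was confined to assignments already released; locating the randomisation off site does not settle this. The exposure is confined to timing of entry, therapist matching, and the PI's own conduct as therapist and supervisor. Blinded assessment of the primary outcome is not contradicted. The size of any bias cannot be estimated from the document, and nothing here shows that the access was used. The conclusion rests on the article's wording alone and assumes that access means the ability to read the list.

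**What to change.** **What the design should have specified.** The list is held only by the external randomising site. Each assignment is released singly, after baseline is recorded, to a coordinator with no therapist role. The PI has no access.

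**What can still be done.** The Trial status section reports the therapy processes complete by the end of March 2019, so removing access now cannot restore concealment at entry. The useful steps are:

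1. Remove the PI's access until the analysis is finished.
2. Check the repository access log, if there is one.
3. Establish with the external site whether the list held future assignments or only released ones.
4. Replace the unqualified concealment and PI-blinding claims with a statement of who could read the list and when.

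Step 4 is the essential one. The cost is one change of access rights, one enquiry and a sentence or two of text; no participants or staff are needed.

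**Optional.** A sensitivity analysis without the PI's own clients would address only effects of the PI as therapist. It does not test selection, since foreknowledge could affect any therapist's clients. If the PI is one of the 11 clinicians and caseloads are equal, it drops about 68/11 ≈ 6 participants, a loss of precision in a trial whose stated power for LH is already only 50%.
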